- To demonstrate an additional benefit of MRI in comparison to SPECT with correct results of MRI (according to the gold standard) where SPECT showed false diagnoses- To compare the performance of SPECT and MRI using conventional diagnostic measures: sensitivity, specificity, positive and negative predictive value- to compare the performance of SPECT and MRI in subgroups of male and female and obese (BMI ≥ 28 kg/m^2^) and non-obese (BMI <28 kg/m^2^) patients- to evaluate the inter-rater reliability in SPECT assessment, MRI-assessment and CPA/CTPA assessment between local in-place read and blinded read- to compare SPECT and MRI regarding safety and procedure related limitations.

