### Patients

The inclusion criteria are chosen to reflect exactly the clinical setting in the diagnostic algorithm for CTEPH. Here, MRI is positioned for an in-place validation compared to SPECT without any exclusion of subgroups compared to SPECT, except for inability to undergo MRI and pregnancy (see Table 1).

**Table 1 T1:** Patient inclusion and exclusion criteria.

Inclusion	• Transthoracic echocardiography suggests pulmonary hypertension
	• Patients with clinical suspicion for CTEPH, scheduled for SPECT
	• Provided informed consent for the study
	• Age >18 years
Exclusion	• Inability to undergo MRI (e.g., due to claustrophobia, cardiac pacemaker, hypersensitivity to MR i.v. contrast imaging agents)
	• Women who are pregnant or breast feeding

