### Blinded-Reader Assessment

A centrally organized blinded reader assessment of SPECT and functional MRI will be implemented to ensure that no information carry-over occurs from clinical SPECT diagnosis to the functional MRI diagnosis or vice versa. Therefore, this blinded reader assessments will be used for the primary analysis. All SPECTs and functional MRIs will undergo a blinded read where independent expert readers are randomly selected for each center and each imaging method from one of the other centers. The second reader is not aware of the findings from the initial in-place read and the respective other imaging method but has access to the patient‘s clinical information used in the in-place SPECT read. Additional to ensuring a truly blinded assessment of the imaging methods, the standardized blinded reader assessment allows assessing inter-rater agreement and context sensitivity of the diagnostic evaluations. If there is a discrepancy between the in-place read and the second reader, a final consensus read will be performed by a third expert reader.

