Secondary analyses will be performed in line with primary analyses using point estimates and 95% Wilson confidence intervals for the various proportions of interest. Safety endpoints will be evaluated descriptively with absolute and relative frequencies of complications and malfunctions of MRI and SPECT and will be compared using risk differences and the Chi^2^-tests. As sensitivity analyses, the primary analysis will be repeated in the per-protocol population based on the blinded reader assessment, comprising all patients without missing co-primary endpoints. Additionally, a sensitivity analysis will be conducted in the per-protocol population based on the in-place assessment, comprising all patients, where in-place MRI diagnosis has been entered into the eCRF before SPECT assessment so that the blinding can be considered to be intact.

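### Safety and procedure endpoints of MRI and SPECT come from the same patients, but the stated chi-square tests, as usually understood, assume independent groups

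*Protocol article*

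**What the plan says.** The trial is paired by design. Eligible patients are "Patients with clinical suspicion for CTEPH, scheduled for SPECT", and the study MRI is added to that work-up. For reading, "All SPECTs and functional MRIs will undergo a blinded read". The expected diagnostic table (Table 2A) cross-classifies the two tests within the same 1000 patients.

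The Objectives section lists a comparison of the two tests on safety and procedural limitations as a secondary objective. Outcome Measures spells out the endpoints: allergic reactions and other adverse events, non-completed procedures, non-diagnostic procedures, the reasons for both, and image quality.

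The Statistical Analysis section then fixes the method: "Safety endpoints will be evaluated descriptively with absolute and relative frequencies of complications and malfunctions of MRI and SPECT", and these "will be compared using risk differences and the Chi^2^-tests". For the other secondary endpoints: "Secondary analyses will be performed in line with primary analyses using point estimates and 95% Wilson confidence intervals for the various proportions of interest". A further secondary objective is "To compare the performance of SPECT and MRI using conventional diagnostic measures: sensitivity, specificity, positive and negative predictive value".

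**The concern.** A chi-square test on a two-by-two table of test (MRI or SPECT) against outcome (failed or not) treats 1080 patients as two separate groups of 1080. Its variance leaves out the covariance between the two results in one patient. That covariance need not be zero: a breathless or restless patient may do badly on both scans.

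Failure and non-diagnostic rates bear on whether MRI can stand in for SPECT. The article's section on the need for a trial itself recalls moderate test performance and modest patient compliance in an earlier multicentre MR angiography study. With positive correlation, the unpaired test is less able to show a real excess of MRI failures, which is the unhelpful direction for a replacement claim.

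**Working it through.** **1. The plan's own figures, to locate the problem.** Inputs from Sample Size and Table 2B: 98% expected against 95%, and 6% expected against 10%; one-sided type I error 2.5%; power 80%. The one-sample formula is

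n = [1.96·√(p0·q0) + 0.842·√(p1·q1)]² / (p1 − p0)².

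- Co-primary 1 (p0 = 0.95, p1 = 0.98): 330.02, rounded up to 331. Total 331/0.58 = 571.
- Co-primary 2 (p0 = 0.10, p1 = 0.06): 387.96, rounded up to 388. Total 388/0.36 = 1078, stated as 1080.

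These match. Each co-primary endpoint is one MRI proportion set against a fixed limit, so pairing does not enter and a Wilson interval is right: 324/331 gives 95.7% to 99.0%, and 23/388 gives 4.0% to 8.7%.

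**2. True size of the unpaired test on paired data.** Let both tests have the same failure rate p, with within-patient correlation φ, in n patients. The true variance of the difference is 2p(1 − p)(1 − φ)/n. The chi-square test uses 2p(1 − p)/n. The true two-sided size of a nominal 5% test is therefore 2·[1 − Φ(1.96/√(1 − φ))]. The article gives no φ, so a range is assumed:

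| φ (assumed) | true SE / SE used | true size |
|---|---|---|
| −0.05 | 1.025 | 0.056 |
| 0 | 1.000 | 0.050 |
| 0.1 | 0.949 | 0.039 |
| 0.3 | 0.837 | 0.019 |
| 0.5 | 0.707 | 0.006 |

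**3. What this does to p-values (rates assumed, n = 1080).** Let b and c be the numbers of patients failing only MRI and only SPECT. McNemar's z = (b − c)/√(b + c). The chi-square z = D/√(2·p̄·(1 − p̄)/n), where D is the difference and p̄ the mean of the two rates.

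- 5% against 3%, with 2% failing both (φ about 0.5): b = 32.4, c = 10.8. McNemar z = 21.6/√43.2 = 3.29, p = 0.001. Chi-square z = 0.02/√(2·0.04·0.96/1080) = 2.37, p = 0.018.
- 2% against 1%: chi-square p = 0.056 whatever the overlap. McNemar p = 0.056, 0.045, 0.024 and 0.009 for φ = 0, 0.1, 0.3 and 0.5.
- 4% against 2.5%, no patient failing both: b = 43.2, c = 27. McNemar z = 16.2/√70.2 = 1.93, p = 0.053. Chi-square p = 0.049. Here the unpaired test is slightly liberal.

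**4. Accuracy, for illustration only.** The plan proposes no interval for an MRI minus SPECT difference. Table 2A shows what pairing would contribute if one were formed. Scale its cells by 1.08, with paired SE = √[(b + c) − (b − c)²/n]/n and unpaired SE = √(p1q1/n + p2q2/n), where b and c now count patients whom only MRI or only SPECT classifies correctly.

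- Specificity, 92% against 90%, n = 432, discordant 29 and 21 before scaling: paired SE 1.70 points, unpaired 1.95 (ratio 1.15).
- Sensitivity, 97% against 96%, n = 648, discordant 20 and 14 before scaling: paired SE 0.93 points, unpaired 1.02 (ratio 1.09).

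**The case against.** The label is not decisive. McNemar's statistic has a chi-square form, and Sample Size uses the same label for what step 1 shows to be a one-sample calculation. The safety evaluation is called descriptive, no success criterion depends on it, and the point estimate of the risk difference is the same paired or unpaired when both tests share a denominator. The overlap is assumed too: nothing in the article supports φ near 0.5, and patients unable to undergo MRI are excluded at entry. All of this stands as a limit on the size of the problem. It does not remove it. In a comparison of two sets of rates, an unqualified chi-square test will be read as the independent-groups test, and the sentence that calls the evaluation descriptive goes on to plan tests.

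A reader might infer more, in three ways that the article does not support.

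- That the Wilson intervals are wrong. Each is valid for its own proportion, whatever the other test showed in the same patients.
- That sensitivity and specificity will be compared by an unpaired method, with intervals 9% and 15% too wide. The chi-square sentence covers only safety endpoints, and those percentages describe difference intervals that the plan never proposes. Not naming a difference interval is a detail that an analysis plan may supply. Outcome Measures also asks for MRI results within each combination of SPECT and gold standard, which retains the paired information.
- That the requirement not to add false positives is left without a valid analysis. Objectives ties success to the co-primary hypotheses, and the one on false positives is the one-sample proportion checked in step 1.

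**Conclusion.** The point holds for the MRI-versus-SPECT tests on safety and procedure endpoints. The stated method, in its usual meaning, does not fit a design in which each patient has both tests. This is a poorly fitting stated method on secondary endpoints, not an omission.

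The error depends on the unknown within-patient correlation. Over the assumed range 0 to 0.5, the true size of a nominal 5% test falls from about 0.050 to 0.006. It vanishes at zero correlation and turns slightly liberal below it. The illustrative p-values rest on assumed rates and overlap, not on figures in the article. The co-primary analyses and the sample size are unaffected.

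**What to change.** In Statistical Analysis, replace the chi-square tests for MRI against SPECT with McNemar's test, exact when events are sparse. State that the risk difference is a paired one, reported with a 95% paired interval (Newcombe or Tango). Apply this to complications, non-completion and non-diagnostic procedures.

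As a free addition for the accuracy objective, report the paired MRI minus SPECT difference in sensitivity and specificity with the same type of interval, beside the separate Wilson intervals. Positive and negative predictive values have different denominators for the two tests, so comparing them needs a method for correlated predictive values, such as generalised estimating equations or a weighted generalised score test.

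The cost is wording in the protocol or analysis plan. It needs no further data or patients.

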### Methods Against Bias

All centers document the age and gender of all patients with suspected CTEPH undergoing SPECT in a screening log. There is agreement that information will be made available in all centers from the hospital administration to assess the degree of representativeness of the investigated patient population for the overall CTEPH-population.

It is the primary aim of this diagnostic study to demonstrate perfect agreement between SPECT and functional MRI in all cases, where the SPECT can be considered to be correct. Therefore, it is of utmost importance that the two diagnostic tests are conducted and evaluated independently. To ensure internal validity of the co-primary endpoint, the diagnoses used in the primary analysis are determined in a standardized blinded reader assessment of the SPECT and MRI images.

Standard operating procedures are developed for each study site in order to achieve that the in-place assessment of MRI and SPECT is performed independently and blinded against each other.

Before commencement of the CHANGE-MRI study at the respective centers, local readers are trained on the basis of ~15 MRI test cases that are provided by the centers to exclude effects of learning curves on the outcome measures.

## Discussion

In this study also Q-SPECT/CT is accepted as an approximation of the VQ-SPECT as reference test, reflecting current clinical practice and real-world test performance, although not in compliance with the current ESC/ERS guidelines (8, 17). This omission of V-SPECT will affect in particular specificity of the reference test in cases of Q-SPECT/CT, for CT cannot be regarded as a fully equivalent substitute for V SPECT.

For primary evaluation, the blinded reader assessment of SPECT and MRI are used to ensure the independency of the assessments and maximize internal validity. On the other hand, external validity of the results might be reduced by the standardized blinded assessment, which does not necessarily reproduce the clinical field of application completely. Consequently, for analyzing the external validity and generalizability of the results based on the primary blinded assessment, the in-place assessments of SPECT and MRI are used as secondary endpoints. While the independence of these assessments cannot be guaranteed, the clinical setting is well represented.

To avoid an increased radiation burden, in this trial the current gold-standard instrument CPA/CTPA is routinely only applied in SPECT-positive patients, which might induce differential verification bias (6, 19, 20). To mitigate this limitation, the follow-up information up to 1 year after study inclusion will be included into the final diagnosis of PE by correcting negative cases, which subsequently are identified as positive in the follow-up period or (although less probable) correcting positive cases, which subsequently are identified as negative.

Ethics votes from the Institutional Review Boards at all participating centers were obtained. The CHANGE-MRI study is designed so that no extra radiation in addition to the clinically indicated radiation-based imaging tests is applied to the study participants. Thus, approval by the Federal Office for radiation protection (Bundesamt für Strahlenschutz) was not required.

This study is conducted in compliance with the Declaration of Helsinki, ICH-E6-guidance, and for design issues regarding diagnostic validation studies, and the EMA Guideline on the Clinical Evaluation of Diagnostic Agents.

The multicenter CHANGE-MRI study could pave the way for lung MRI methods to be an equal rights alternative to VQ-SPECT in the diagnostic pathway for CTEPH. By generating robust evidence both from in-place assessments and a standardized blinded reader assessment, this trial will generate the data needed for a thorough comparison of SPECT and MRI technology.

## Abbreviations

BREATH: Biomedical Research in Endstage and Obstructive Lung Disease Hannover
CPA/CTPA: catheter pulmonary angiography or computed tomography pulmonary angiography
CTEPH: thromboembolic pulmonary hypertension
DCE: dynamic contrast-enhanced
MHH: Hannover Medical School
MRI: magnetic resonance imaging
LGMLC: Universities of Giessen and Marburg Lung Center
PE: pulmonary embolism
Q-SPECT/CT: perfusion single-photon emission computed tomography
TLRC-H: Comprehensive Pneumology Center Munich and the Translational Lung Research Center Heidelberg
USFD: University of Sheffield
V-SPECT: ventilation single-photon emission computed tomography
VQ-SPECT: ventilation–perfusion single-photon emission computed tomography.
